## Abstract

**Trial registration:**

ClinicalTrials.gov Registration: NCT06251635

## Introduction

Antipsychotic (AP) medications carry an adverse metabolic side effect profile which significantly increases the risk of developing type 2 diabetes and cardiovascular disease by 3–5-fold in patients using these medications compared to the general population.[1–6] These adverse effects accrue early during treatment; alarmingly high rates of dyslipidemia (>55%) and prediabetes (>15%) have been reported in first episode patients within 6 months of AP exposure.[7] Of particular concern is that females are disproportionally more affected by these adverse effects than males; [8,9] findings from the CATIE study revealed that the prevalence of metabolic syndrome in patients with schizophrenia spectrum disorder (SSD) was 51.6% among females compared to 36% among males.[10] AP-associated metabolic disturbances are linked to non-adherence, lower self-esteem, and decreased quality of life, [11] and might exacerbate pre-existing cognitive dysfunction in SSD.[12] These cumulative effects significantly increase the illness burden of SSD. Notably, there is evidence to suggest that females with SSD tend to report lower quality of life than males with SSD, despite having less severe course of the illness.[13] It is possible their increased susceptibility for the metabolic side effects of antipsychotics may contribute to the reported lower quality of life than males.

While the pathophysiology of these effects remains unclear, brain insulin resistance (IR) is posited to be an important determinant [14,15]. Insulin receptors are widely expressed in the brain and bear on multiple physiologic processes [14]. For instance, insulin, separate from its effects in the periphery, regulates hepatic glucose production through insulin receptors in the hypothalamus. Using the pancreatic euglycemic clamp technique to separate central and peripheral insulin effects, it has been established that an intracerebroventricular (ICV) infusion of insulin in male rodents results in a decrease in glucose production by the liver [16,17]. Similar findings have been observed in healthy male humans with intranasal insulin (INI) (which is a direct, non-invasive way of delivering insulin to the brain, analogous to ICV infusions in rodents) [18].

Our group has shown that an acute dose of olanzapine (OLA) can completely abolish this well-established ability of a central insulin stimulus to decrease hepatic glucose production in male rats [19]. This suggests that antipsychotics have a direct anti-insulin action *in the brain* that is independent of weight gain. Despite reported sex differences in the effects of brain insulin on energy balance in the literature where males are believed to be more sensitive to the catabolic actions of insulin than females [20,21], this finding is yet to be explored in females. Preclinical evidence has demonstrated that ICV infusion of insulin decreases food intake and body weight in male rats but not female rats, male rats given estradiol, or ovariectomized female rats [22]. This suggests that insulin action in the brain is sex-dependent and requires further sex-focused investigation.

Several neuroimaging studies have employed INI to demonstrate the effects of insulin on the brain. For example, in a study including both sexes, INI enhanced connectivity in the default mode network (DMN), measured using resting state functional magnetic resonance imaging (rs-fMRI) [23]. This ability of INI to induce changes in MRI-based parameters in healthy humans allows it to be leveraged as an assay of insulin action in the brain [24]. Lack of expected responses to an INI challenge is interpreted as a lack of insulin sensitivity. However, these results are primarily based on male-only studies, with a limited number of studies examining only females or both sexes.

To this last point, there continues to be a significant sex bias in our understanding of insulin effects in the brain as most of the research with INI has been conducted in males alone [18,25–30]. In the few studies that have included both males and females, differential effects according to sex have been noted. For example, INI appears to acutely reduce food intake in fasted, normal-weight males, but not females [31]; however, INI has been shown to increase satiety and reduce the palatability of certain foods in females [32]. Similarly, 8 weeks of INI treatment resulted in a significant reduction in body weight and body fat content in males only [21].

A recent report has indicated that brain insulin sensitivity differs between sexes, and this may relate to menstrual phases [33]. Specifically, brain insulin sensitivity in females is higher and comparable to lean males during the follicular phase (i.e., right before ovulation when estrogen levels are high) than during the luteal phase (i.e., after ovulation when both estrogen and progesterone levels are high) [33]. and this may contribute to the well-established decrease in whole-body insulin sensitivity in the luteal phase [34,35].

There has yet to be a study that investigates AP-induced insulin resistance in females and the impact of menstrual cycle factors on this relationship. Preclinical evidence of AP-induced disruption in brain insulin action was in male rats only, and previous work aimed at translating these findings did not investigate the effect of menstrual phase [24] It is therefore critical to study the effect of APs on brain insulin action in females, and to examine how it fluctuates with the menstrual cycle.

## Objectives and hypotheses

In this study, we seek to address a significant gap in the literature by investigating 1) how brain insulin action differs in females according to their menstrual cycle phase, and 2) how a high metabolic liability agent such as OLA might interrupt these differential insulin effects. We have chosen to conduct this study in healthy volunteers to minimize confounding effects of psychiatric disorders on glucose metabolism [36]. OLA was selected as a representative antipsychotic due to its well-established metabolic liability [37]. An acute dosing paradigm (i.e., two days of dosing) is employed to avoid longer-term changes in adiposity [38]. thereby allowing for a more precise assessment of whether antipsychotics exert direct effects on brain insulin function.

Resting state functional activity and connectivity (rsFC) will be used as a neural signature of brain insulin action. We hypothesize that 1) INI, but not intranasal placebo (INP), will modulate resting state activity in the brain in females during the follicular phase of their menstrual cycle but not the luteal phase; 2) Oral OLA will inhibit all INI-induced effects, relative to oral placebo (PL) during the follicular phase. OLA will have no apparent effect in the luteal phase given pre-existing brain IR.

## Methods and materials

The study is a single centre clinical trial conducted at the Centre for Addiction and Mental Health (CAMH), a psychiatric teaching hospital in Toronto, Canada. It has been granted full ethics approval by the CAMH Research Ethics Board (REB Protocol #127/2023, Version #5, 11-October-2024; S1 File). This study is also approved under the purview of Health Canada and has been registered with ClinicalTrials.gov (NCT06251635). The Standard Protocol Items: Recommendations for Interventional Trials (SPIRIT) schedule of enrolment is reported in Fig 1. The SPIRIT checklist is available in S2 File.

**Fig 1 pone.0352262.g001:**
[figure not shown]
SPIRIT schedule of enrollment, interventions, and assessments.

### Study design

Fig 2 provides a comprehensive overview of the entire study design and protocol. In a single-blind crossover study, every participant is given four different treatment conditions (INP/PL, INI/PL, INP/OLA, or INI/OLA) on two separate occasions. This means that each treatment is administered once during each menstrual cycle phase, resulting in participants receiving all conditions twice over the course of the study. All participants will receive oral PL at visit 1 and oral OLA at visit 2 of each cycle phase. Study visits will take place 2–6 weeks apart to ensure specific menstrual phase across the four visits and adequate washout between conditions. Participants will undergo two visits during the follicular phase of the menstrual cycle. To ensure a regular menstrual cycle, participants will be asked to provide information about the length of their last three cycles. Average cycle duration will be calculated to determine cycle phases. One cycle duration is defined as from cycle onset date (Day 1) to the day before the next cycle onset (i.e., Day 1 is defined as the first day of menstruation). Based on this, participants will be invited to complete the visits during the specific windows of their follicular and luteal phase. Menstrual cycle phases will be identified using calendar-based counting. The onset of their menstruation will be considered as the first day of the current menstrual cycle and will be denoted the start of the follicular phase. The follicular phase visit can take place starting 2 days after the start of the current menstrual cycle and no more than 17 days apart from the start of the subsequent cycle (i.e., they will be scanned between days 3 and 11 of their cycle). The luteal phase will be defined in the time frame of a maximum of 10 days but no less than 3 days before the start of the subsequent cycle (i.e., between day 18–25). Measurement of serum sex hormones (progesterone, estrogen, luteinizing hormone (LH) and follicular stimulating hormone (FSH)) will be done at each visit to confirm cycle phase.

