### Study participants

This study will recruit fifteen healthy female volunteers aged 18–35 years, of any race or ethnicity, with normal body mass index (BMI 18.5–25 kg/m²) and regular menstrual cycles. Participants will be excluded from the study for the following reasons: 1) History of psychiatric illness (the Mini International Neuropsychiatric Interview (MINI) will be used to screen for psychiatric illness in the present or past), 2) Pre-diabetes or diabetes (fasting glucose ≥6.0 mmol/L, HbA1c>6% or use of any anti-diabetic drug), 3) Evidence of impaired insulin sensitivity, assessed using the Homeostatic Model Assessment for Insulin Resistance (HOMA-IR) ≥1.8 [42,43], 4) Family history of diabetes in a first degree relative (parent or sibling), 5) Use of weight reducing agents, 6) History of kidney or liver disease, 7) Moderate-to-severe substance use, 8) Irregular menstrual cycles (e.g., menstruation occurs less than 21 days or more than 35 days apart, or not having menstruated for three months (or 90 days), or conditions such as endometriosis or polycystic ovary syndrome (PCOS), or prior surgical interventions such as a hysterectomy or oophorectomy), 9) Use of hormonal birth control, 10) Current use of progesterone, estrogen, testosterone, or fertility treatment, 11) Pregnant or breastfeeding, 12) Major medical or surgical event within the last 6 months, 13) Any condition that interferes with safe acquisition of MRI data such as metal implants, pacemakers, cochlear implants, claustrophobia, etc., 14) Any contraindications to the investigational products as listed in the product monographs including known hypersensitivity to the drug or the excipients of the product (note: enzymatic lactose intolerance is NOT exclusionary), 15) Use of any of the prohibited medications listed in the product monograph of olanzapine (e.g., Levodopa and dopamine agonists and antihypertensive agents).

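### The follicular scan rule contradicts its own bracketed day range, and both bracketed ranges fit only one of the eligible cycle lengths

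*Protocol article*

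**What the plan says.** All of the window wording is in the Study design section of the protocol article. The lower follicular bound is clear: "The follicular phase visit can take place starting 2 days after the start of the current menstrual cycle". The other bound, with its bracketed explanation, is "no more than 17 days apart from the start of the subsequent cycle (i.e., they will be scanned between days 3 and 11" of the cycle. The luteal visit is set at "a maximum of 10 days but no less than 3 days before the start of the subsequent cycle", explained as "i.e., between day 18–25".

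The same section fixes the day count: "One cycle duration is defined as from cycle onset date (Day 1) to the day before the next cycle onset". Phases are identified by calendar counting, using the participant's average over her last three cycles, and sex hormones are measured at each visit to confirm the phase.

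The Study participants section excludes a woman whose "menstruation occurs less than 21 days or more than 35 days apart", so cycle lengths from 21 to 35 days are eligible.

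The Statistical analysis section makes intranasal condition x phase the effect of interest in the first model, and intranasal x oral x phase the effect of interest in the second.

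**The concern.** The windows decide when each scan takes place, and therefore which level of the phase factor its data represent. Here the follicular rule and its explanation point to nearly opposite parts of the cycle. Both explanations are introduced as equivalent to the rule rather than as an example, although they are fixed calendar days and the rules count back from an onset date that varies between women.

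Two staff members could each follow part of the text faithfully and schedule different visits. If visits are mis-timed, the follicular–luteal contrast becomes less clean, and both primary interactions would tend to be pulled toward zero. The trial has 15 participants and two visits per phase for each, which leaves little room for that.

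**Working it through.** **Inputs.** Let L be the cycle length and N the day number of the next onset. By the article's own definition N = L + 1. Simple subtraction uses N = L. I ran both counts for L = 21 to 35. For scan day d:

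- follicular as written: d ≥ 3 and N − d ≤ 17
- follicular with the inequality reversed: d ≥ 3 and N − d ≥ 17
- luteal: 3 ≤ N − d ≤ 10

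**Reproducing the bracketed ranges.** The follicular rule as written does not yield days 3–11 at any eligible length. With the inequality reversed, both brackets come out exactly, at one length only:

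- simple subtraction, L = 28: 28 − 17 = 11, 28 − 10 = 18, 28 − 3 = 25
- the article's count, L = 27 (N = 28): the same three results

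**Follicular rule as written.**

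- At L = 28, d ≥ N − 17 gives day 12 onward (29 − 17) by the article's count, or day 11 onward (28 − 17) by subtraction. The overlap with days 3–11 is 0 or 1 of 9 days.
- Day 3 qualifies only if N ≤ 20. The smallest eligible N is 21 by subtraction and 22 by the article's count, so day 3 never qualifies.
- Any day that is 3 to 10 days before the next onset is also 17 or fewer days before it. The written follicular window therefore contains the whole luteal window at every eligible length (days 19–26 at L = 28 by the article's count).

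**Luteal rule against days 18–25.** The first figure in each cell uses the article's count, the second simple subtraction.

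| Cycle length | Luteal rule gives | Days shared with 18–25 (of 8) |
|---|---|---|
| 21 | 12–19 / 11–18 | 2 / 1 |
| 28 | 19–26 / 18–25 | 7 / 8 |
| 32 | 23–30 / 22–29 | 3 / 4 |
| 35 | 26–33 / 25–32 | 0 / 1 |

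**If the inequality is reversed.** The follicular window needs at least 17 days to the next onset and the luteal window at most 10, so the two rules cannot overlap. A day meets both phases only if one phase is taken from the rule and the other from the bracket:

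- article's count: day 18 at L = 34, and days 18–19 at L = 35
- simple subtraction: day 11 at L = 21, and day 18 at L = 35

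Most other bracketed days that miss their rule fall in neither window. By the article's count these include days 18–22 at L = 32, days 20–25 at L = 35 and, for the follicular bracket, days 6–11 at L = 21.

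**The case against.** The strongest reply is that the intent is recoverable. The same sentence opens the window at day 3, and the bracket fits a rule of at least 17 days, so the inequality looks like a slip. Scheduling uses each woman's own average cycle, and staff ask for her latest period date about a week before each visit (Study visits 1–4), which suggests the brackets are only a gloss. Hormones are measured at every visit, and the Screening visit section ties the luteal phase to high progesterone, which would catch some errors. All of this stands, and it limits the size of the problem. It does not settle the text. The article never says whether rule or bracket governs, and its marker for the follicular phase, high estrogen, is described in the Introduction as also present in the luteal phase. Missing assay cut-offs are not held against it, since the full protocol may carry them.

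A reader might infer three stronger things that the article does not support.

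- *That both windows contradict themselves.* The outright contradiction is follicular only. The luteal rule is sound, and its bracket is merely not general.
- *That the same scan day can routinely count as either phase.* That holds across the luteal window only under the literal inequality. On the likely intended reading it is confined to mixing rule and bracket at about 21 or 34–35 days.
- *That a definite loss of power follows.* The article gives no mis-timing rate and states that no formal power calculation was done. Suppose 20% of luteal visits carried the full follicular effect, and treat the cited range d = 0.8 to 1.4 as a per-visit effect d_z. With n = 15, a two-sided 5% paired test and interaction effect (1 − 0.20) x d_z/√2, power falls from 0.53 to 0.37 at one end and from 0.95 to 0.81 at the other. Both the rate and the effect are invented inputs. Since most misfitting days belong to neither phase, the full dilution is not established either.

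**Conclusion.** The point holds as an error in an operative rule. As written, the follicular bound and its explanation share at most one day in a 28-day cycle, the stated first day is never allowed, and the luteal window lies wholly inside the follicular one. Separately, both day ranges hold for one eligible cycle length out of the fifteen from 21 to 35 days. These results need only the article's own definitions and are the same in substance under either day count.

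The effect on the primary interactions is directional: dilution if visits were mis-timed. Its size cannot be derived from the article, and nothing in it shows that any visit has been mis-timed. The text still needs correcting, because phase enters both primary terms and visits are continuing.

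**What to change.** Reconcile the Study design wording into one rule per phase, expressed relative to each participant's own expected next onset and using one stated day count. Remove the conflict between the follicular inequality and its bracket. Delete the fixed day ranges, or label them as an example for a single named cycle length.

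Then audit the visits already completed against the reconciled rule, using the recorded onset dates and the hormone values measured at each visit, progesterone in particular. Flag visits that do not conform, and run both primary models with and without them as a sensitivity analysis.

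The cost is a wording amendment and a desk audit of data already held, with possibly a few visits flagged. The Recruitment status section reports six completers and others still attending, so the correction can still guide the remaining visits.

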**Fig 2 pone.0352262.g002:**
[figure not shown]
Summary of overall study design and visit protocol. Following screening, eligible participants will be enrolled to take part in the 2x2 crossover study. Each participant will undergo a total of four primary study visits, two per cycle phase (follicular and luteal). Participants will receive oral placebo (PL) on days 0 and 1 of the first visit of each phase, and oral olanzapine (OLA) on days 0 and 1 of the second visit of each phase. At each visit, intranasal placebo (INP) will be administered prior to scan #1, and intranasal insulin (INI) prior to scan #2. Figure created on BioRender.com.

Each of the study periods will involve a three-day protocol (Fig 2): administration of OLA 5 mg (or PL) HS on day 0, OLA 10 mg (or PL) HS on day 1, and cognitive testing and MRI scanning on day 2. There will be two MRI scans on day 2, the first following administration of INP and the second following 160 IU of INI. Administration of INP always precedes INI as the effect of insulin in the brain is known to last for 2 hours, and counterbalancing the administration of INI first will require a much longer washout period/study visit, adding participant burden.

The two acute OLA doses of 5 mg and 10 mg are chosen for reasons of practicality and safety in line with previous studies [24,39]. The INI dose is the maximum safest dose that has been administered in humans and is chosen based on earlier work in nine healthy males showing a dose-dependent relationship on regional brain activity, with the strongest effects being observed after 160 IU [27]. This dose has been shown to induce changes in the brain in females as well [40,41]. Blood samples will be drawn before and after the MRI to measure insulin spillover. Dose-dependent spillover of INI into peripheral circulation has been reported, although the observed brain responses were not correlated with this transient rise in circulating insulin [27]. OLA levels will be measured to assess adherence.

### Investigational products

The oral investigational agent used in this study is olanzapine (Generic brand: Apo-Olanzapine), administered at night over the course of two days (5 mg and 10 mg, respectively). The intranasal investigational product will be either Insulin Lispro (Humalog) or placebo (0.9% saline solution) administered via a metered nasal dispenser. A single spray dispenses 0.1 mL (10 IU) of insulin. A single spray is administered in each nostril while inhaling. After waiting 1 minute, another spray is similarly administered in each nostril. The intranasal spray process in both nostrils is repeated for a total of 8 times (total of 160 IU will be delivered). Medication adherence will be monitored by collecting empty medication blister packs and measuring blood levels of OLA. INI/INP will be administered in the presence of study staff.

### Study participants

This study will recruit fifteen healthy female volunteers aged 18–35 years, of any race or ethnicity, with normal body mass index (BMI 18.5–25 kg/m²) and regular menstrual cycles. Participants will be excluded from the study for the following reasons: 1) History of psychiatric illness (the Mini International Neuropsychiatric Interview (MINI) will be used to screen for psychiatric illness in the present or past), 2) Pre-diabetes or diabetes (fasting glucose ≥6.0 mmol/L, HbA1c>6% or use of any anti-diabetic drug), 3) Evidence of impaired insulin sensitivity, assessed using the Homeostatic Model Assessment for Insulin Resistance (HOMA-IR) ≥1.8 [42,43], 4) Family history of diabetes in a first degree relative (parent or sibling), 5) Use of weight reducing agents, 6) History of kidney or liver disease, 7) Moderate-to-severe substance use, 8) Irregular menstrual cycles (e.g., menstruation occurs less than 21 days or more than 35 days apart, or not having menstruated for three months (or 90 days), or conditions such as endometriosis or polycystic ovary syndrome (PCOS), or prior surgical interventions such as a hysterectomy or oophorectomy), 9) Use of hormonal birth control, 10) Current use of progesterone, estrogen, testosterone, or fertility treatment, 11) Pregnant or breastfeeding, 12) Major medical or surgical event within the last 6 months, 13) Any condition that interferes with safe acquisition of MRI data such as metal implants, pacemakers, cochlear implants, claustrophobia, etc., 14) Any contraindications to the investigational products as listed in the product monographs including known hypersensitivity to the drug or the excipients of the product (note: enzymatic lactose intolerance is NOT exclusionary), 15) Use of any of the prohibited medications listed in the product monograph of olanzapine (e.g., Levodopa and dopamine agonists and antihypertensive agents).

Participants can continue to receive routine medical care while enrolled. Any participant may be discontinued from the study at the discretion of the investigators if this is deemed to be in the best interest of the participant. The decision may be made either to protect the participant’s health and safety, or because it is part of the research plan that people who develop certain conditions may not continue to participate. Reasons for withdrawing individual participants from the study may include one or more of the following: a) major protocol violation, b) participant lost to follow-up, c) withdrawal of consent, or d) participant becomes pregnant or breast-feeding.

